## Abstract

Despite advances in the treatment of Alzheimer’s disease (AD), there is currently no prospect of a cure, and evidence shows that multifactorial interventions can benefit patients. A promising therapeutic alternative is the use of transcranial direct current stimulation (tDCS) simultaneously with cognitive intervention. The combination of these non-pharmacological techniques is apparently a safe and accessible approach. This study protocol aims to compare the efficacy of tDCS and cognitive intervention in a double-blind, randomized and factorial clinical trial. One hundred participants diagnosed with mild-stage AD will be randomized to receive both tDCS and cognitive intervention, tDCS, cognitive intervention, or placebo. The treatment will last 8 weeks, with a 12-month follow-up. The primary outcome will be the improvement of global cognitive functions, evaluated by the AD Assessment Scale, cognitive subscale (ADAS-Cog). The secondary outcomes will include measures of functional, affective, and behavioral components, as well as a neurophysiological marker (Brain-derived neurotrophic factor, BDNF). This study will enable us to assess, both in the short and long term, whether tDCS is more effective than the placebo and to examine the effects of combined therapy (tDCS and cognitive intervention) and isolated treatments (tDCS vs. cognitive intervention) on patients with AD.

**Clinical Trial Registration**: www.ClinicalTrials.gov, identifier NCT02772185—May 5, 2016.

## Introduction

Alzheimer’s disease (AD) is characterized by a progressive deterioration of cognitive functions, impacting the autonomy of patients in performing their activities of daily living (ADLs; Buschert et al., 2010). Pharmacological approaches only provide moderate symptom control, provisionally improving cognition or slowing down cognitive decline (Massoud and Gauthier, 2010). In this context, the earlier the diagnosis of probable AD is performed, the better the patient prognosis will be as cognitive intervention can be applied in the early stages of the disease (Fernández-Calvo et al., 2015; Kawashima et al., 2015). For example, memory, executive functions and attention may be relatively improved when adequate support is provided (García-Alberca, 2015). However, intervention specificity, best candidate selection for different types of protocols, and whether benefits can transfer to untrained cognitive domains are still controversial topics (Alves et al., 2013; Fernández-Calvo et al., 2015).

Thus, multimodal intervention makes it possible to prevent (Olanrewaju et al., 2015) or delay the progression caused by the disease (Olazarán et al., 2010). Currently, non-invasive neurostimulation techniques such as transcranial direct current stimulation (tDCS) have been used to delay the cognitive deficits and to decrease the functional impairment of patients with dementia (Andrade et al., 2016; André et al., 2016; Gonsalvez et al., 2017). tDCS is a low-cost, portable and safe tool that induces plasticity via electrical stimulation using a low-intensity current and a continuous flow through the brain. This pattern of electricity modulates cortical activity without directly acting on neurons, which decreases the risk of serious adverse effects (Boggio et al., 2011).

The neurobiological basis of AD recovery after neurostimulation is the ability of tDCS to induce long-term synaptic changes. The effects perceived during stimulation are apparently associated with changes in the subliminal membrane resting levels that modulate the input-output curve. Conversely, prolonged effects would act on GABAergic activity, the glutamatergic system, long-term potentiation (LTP) and long-term depression (LTD) mechanisms related to plasticity (Yu et al., 2015). Studies in mice with a similar disease to AD show tDCS effects on several of these factors, also including axonal activation and alteration in the cellular transmembrane potential, and consequently neurotransmitter balance (Ruohonen and Karhu, 2012).

In a critical review of the use of tDCS combined with cognitive rehabilitation, Cappon et al. (2016) concluded that many studies failed to assess whether improvement in a specific task transfers to ADLs in AD treatment. The authors indicate it is imperative to discriminate between increased performance on a specific cognitive task and recovery in more general ADLs demanding that cognitive function. This suggests the importance of including other cognitive domains in both the evaluation and the treatment protocol, such as memory and executive function. Consistent results reported by systematic reviews and meta-analyses have shown that overall cognitive stimulation, a cognitive intervention based on a range of different cognitive activities (Clare and Woods, 2004), promotes better cognitive and neuropsychiatric benefits in patients with AD than cognitive training of specific domains (e.g., memory; Buschert et al., 2010; Spector et al., 2012; Woods et al., 2012; Bahar-Fuchs et al., 2013; Huntley et al., 2015).

Nevertheless, some studies only evaluated the effect of different forms of neurostimulation without associating neurostimulation with cognitive intervention protocols (Boggio et al., 2009, 2011; Bystad et al., 2016b). To date, three studies have evaluated the combined use of tDCS and cognitive rehabilitation (Cotelli et al., 2014; Penolazzi et al., 2015; Andrade et al., 2016). A common limitation to these studies is the use of a brief protocol of tDCS (only 10 sessions), without long-term follow-up of participants (longer than 6 months). Because AD is a progressive disease, monitoring participants for long periods of time is crucial to assess whether the therapeutic effect is sustained to enable the tested protocol to be transferred to clinical practice. However, a thorough search of the relevant literature yielded no articles analyzing tDCS efficacy associated with cognitive intervention in producing physiological and behavioral changes in patients over time (12 months).

Additionally, the current application moment, meaning whether it is applied before, during, or after cognitive intervention, may also cause variability in the results (Cappon et al., 2016). In a systematic review and meta-analysis assessing the effects of non-invasive neurostimulation on healthy elderly individuals and patients with AD, the authors observed that “the optimal timing for administration of tDCS” varies according to the physiological and pathological aging (Hsu et al., 2015). The use of neurostimulation before task execution can produce robust effects on healthy elderly individuals. Conversely, AD group shows more pronounced effects for studies that apply the stimulation during task execution compared to studies that uses the stimulation before task execution.

Another key point is that most studies involving tDCS in AD typically assess neurostimulation effects on only one cortical area. This aspect is worrying because the pathological characterization of dementia differs from other neurological diseases, wherein only one brain region should be modulated such as stroke or depression (Iannone et al., 2016; Ilić et al., 2016). In AD, the clinical symptoms are not restricted to memory loss, suggesting the involvement of more complex neural networks (Lesuis et al., 2016; Ossenkoppele et al., 2016). Thus, choosing only the frontal or temporal region could limit the scope of treatment and result in the absence of cognitive gains, as found by Bystad et al. (2016a) who observed no improvement in the cognitive domains of patients when applying tDCS over a short period (10 days) exclusively on the left temporal cortex. Thus, it is important that the therapeutic protocol of tDCS in AD should encompass another cortical locus.

Related to this, other factors must be analyzed such as the stimulation duration. Although the standard tDCS protocol only involves application in one cortical area per session of 20 min (Nitsche et al., 2008), some authors also reported that 10 min of tDCS application in one (Drummond et al., 2017) or two cortical regions, one after the other (frontal and parietal cortex; Jones et al., 2015), is sufficient to promote neuromodulatory effects. In addition, Fricke et al. (2011) prove that the use of repeated applications of tDCS generates long-lasting effects.

Although there are several studies involving non-invasive neurostimulation and cognitive training in the treatment of AD, the cognitive and functional effects remain unclear. Recent reviews suggest larger samples to investigate the synergistic effects of these two therapies, with control of confounding variables and with realistic parameters, aimed at clinical practice (Hsu et al., 2015; Zhao et al., 2017).

Accordingly, we propose that stimulating different brain regions specifically related to the neuropathology of AD along with repeated applications of 10-min tDCS in each session may be an option to achieve short- and long-term effects. However, at this time we have only just drawn up a study protocol and these hypotheses can only be tested in the main clinical trial that we aim to perform. In addition, no reports of factorial randomized clinical trials using with tDCS and cognitive intervention stimulating different cortical regions with a 10-min interval in each, and with follow-up for AD-related outcomes have been found to date.

In this way, we designed the Neurostimulation combined with Cognitive Intervention in AD (NeuroAD) clinical study, a phase II/III trial, to address the safety and efficacy of tDCS and cognitive intervention in the treatment of AD. Based on the aforementioned data, which suggest beneficial effects of both cognitive intervention and tDCS on patients with AD, we hypothesize that combining both treatments modulates cortical activity and improves the long-term clinical symptoms of patients, manifested as increased cognition and functional capacity and reduced affective and behavioral changes.

## Materials and Equipment

### Overview

NeuroAD is a factorial, placebo-controlled, double-blind and randomized clinical trial in which 100 patients at the mild stage of AD are randomly assigned to four groups: 1—active tDCS and active cognitive intervention; 2—sham tDCS and active cognitive intervention; 3—active tDCS and placebo cognitive intervention; and 4—sham tDCS and placebo cognitive intervention. All of the patients will be subjected to tDCS and cognitive intervention applied for 24 workdays. At the end of the trial, patients who received active tDCS and achieved clinical response will be invited to maintain tDCS bimonthly for 12 months, as part of a long-term study of tDCS for AD; those who did receive sham tDCS and did not respond will be offered 24 open-label daily sessions of tDCS (crossover study); finally, those who showed response with cognitive intervention (real or placebo) and sham tDCS will be referred to other neuropsychological centers specialized in treating dementias in our Institution.

### Randomization and Blinding

The participants will be randomized into 1:1:1:1 blocks using the random number generator of an open-access randomization software program^1^. This sequence will be remotely performed by a blind researcher not involved in other research procedures. After the randomization process, a blinded staff member will perform patient allocation between the groups. Hidden allocation will be performed with closed, sealed and sequentially numbered envelopes. The participants will be identified by codes and will also be blinded; that is, they will ignore the arm of the study to which they will be allocated. The evaluation and treatment will be performed by independent researchers, who will identify the patients by their respective codes and will be blinded to the other research procedures. Data analysis will be performed by a professional not involved in any stage of patient recruitment, screening, assessment, or intervention. The effectiveness of the masking will be assessed after completing the treatment by interviewing the raters, who will be asked what type of treatment (active or placebo) they believe that the patient received. The relatives of participants will also be blinded and asked, at the end of the treatment, to which group they believe that the patient was allocated. The patients will also be asked questioned about which group they believe have been allocated. We decided to assess the effectiveness of the blinding by asking the relatives and/or caregivers of the patients because the patients have mild AD.

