Considering the different evaluations with the same cognitive tests throughout the clinical trial, the improvement in the performance of these tests may result from practice and not from the intervention applied (Chelune, 2010; Goldberg et al., 2015). A RCI will be used; it serves to assess whether the changes identified comparing pre- and post-intervention data can be attributed to the procedures used or are mere oscillations, artifacts, or measurement errors (Jacobson and Truax, 1991) resulting from repeated practice effects (Chelune et al., 1993). The RCI, correcting for practice effects and using the Iverson’s standard error of the difference will be calculated based on the Duff’s (2012) formulae.

The follow-up analysis will calculate the primary outcome (i.e., a decline in cognitive state). As proposed in Phase 1, the same cutoff will be used to classify clinical improvement (3.76 points in the mean, with an SD of 1.33 points in the ADAS-cog). The primary outcome measure will be calculated considering the differences between clinical improvement and clinical relapse (or censored if relapse did not occur). Kaplan-Meier survival analysis will be used to calculate this outcome. To investigate interactions of risk factors, the following variables will be observed: demographics characteristics (age, gender, level of education), clinical condition (duration of illness, comorbidities and neuropsychiatric states) and “methodological” variables (Phase 1 group and crossover). The hazard ratio will be estimated using the Cox proportional hazards (to each predictor variable or covariate)”

Regarding safety, adverse effects will be analyzed in terms of the ratio in each group and period (before and after treatment) and analyzed using Fisher’s exact test. Multivariate regression will be used to identify predictors of response. The outcome variables will be tDCS and cognitive intervention, and the predictors will be age, gender, comorbidities and use of medication.

The effectiveness of the blinding will be analyzed by using the chi-square test, comparing the ratio between errors and correct responses. Furthermore, these tests will be compared between patients with clinical response and those who failed to improve.

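### The raters' active-or-placebo guess has no defined correct answer for the 50 of 100 patients who receive one active and one placebo component

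*Protocol article*

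**What the plan says.** All statements are in the protocol article.

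- **Design (Overview).** There are four groups. Groups 1 and 4 receive both components active and both placebo, respectively. The other two are mixed: "2—sham tDCS and active cognitive intervention" and "3—active tDCS and placebo cognitive intervention".
- **Size (Sample Size; Randomization and Blinding).** 25 patients per group, 100 in total, allocated 1:1:1:1.
- **Question to raters (Randomization and Blinding).** After treatment they are "asked what type of treatment (active or placebo) they believe that the patient received".
- **Question to relatives and patients (same section).** Relatives are "asked, at the end of the treatment, to which group they believe that the patient was allocated". For patients: "The patients will also be asked questioned about which group they believe have been allocated".
- **Analysis (Proposed Analysis).** A chi-square test "comparing the ratio between errors and correct responses". The results are then compared between patients with and without clinical response.

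The article does not say whether the raters' answer refers to tDCS, to the cognitive intervention or to both. It does not say which answer counts as correct in groups 2 and 3.

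**The concern.** A two-way active-or-placebo question suits a two-arm trial. Here it leaves half the sample without a right answer: for a patient on sham tDCS with active cognitive intervention, each answer is true of one component and false of the other. The analysis needs every answer to be classed as an error or as correct, so someone must choose a key, and the result can change with that choice.

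A key added later does not solve this fully. A single answer does not show which component the rater had in mind, and that is lost at the interview.

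What is at stake is the evidence that raters were blind. Stepwise Procedures has treatment-blinded investigators carry out the outcome assessments, and the CSDD is described as clinician-administered. The trial aims to separate the effects of tDCS and cognitive intervention, so a reader of those outcomes would want to know which component, if either, the raters had identified. The planned comparison by clinical response inherits the same ambiguity.

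**Working it through.** **Inputs.** 25 per group and four groups (Sample Size, Overview). The article gives no figure for the blinding check itself, so there is none to reproduce beyond the sample: 4 × 25 = 100, and groups 2 and 3 together are 2 × 25 = 50, or 50%.

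**Step 1: raters who know tDCS and nothing else.** This is a hypothetical case. They answer active in groups 1 and 3 and placebo in groups 2 and 4.

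| Key for the correct answer | Groups scored correct | Correct |
|---|---|---|
| tDCS received | 1, 2, 3, 4 | 100/100 |
| Any component active | 1, 3, 4 | 75/100 |
| Cognitive intervention received | 1, 4 | 50/100 |

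**Step 2: partial knowledge.** Assume, for illustration only, that raters answer active for 20, 5, 20 and 5 of the 25 patients in groups 1 to 4. Cross-tabulate guess against the coded truth and use the Pearson chi-square without continuity correction, N(ad − bc)² / (product of the four margins).

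- tDCS key, rows 40/10 and 10/40: 100 × (1600 − 100)² / 50⁴ = 36.0, p = 2 × 10⁻⁹; 80/100 correct.
- Cognitive key, rows 25/25 and 25/25: chi-square 0, p = 1.0; 50/100 correct.
- Any-active key, rows 45/30 and 5/20: 100 × (900 − 150)² / (75 × 25 × 50 × 50) = 12.0, p = 0.0005; 65/100 correct.
- Both-active key, rows 20/5 and 30/45: 12.0, p = 0.0005; 65/100 correct.
- Groups 2 and 3 dropped, rows 20/5 and 5/20: 50 × (400 − 25)² / 25⁴ = 18.0, p = 2 × 10⁻⁵; 40/50 correct.

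If the guesses follow the cognitive intervention instead (20, 20, 5, 5), the first two results swap and the other three are unchanged. So the same answers can indicate strong unblinding or none, and the last three keys cannot show which component was recognised.

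**Step 3: relatives and patients.** Reading their question against the four groups, an answer is right or wrong for all 100 patients, with chance at 1/4 = 25%. It also contains a guess for each component. Suppose a respondent always identifies the cognitive component and guesses tDCS at random. The expected proportion correct on group is 1 × 1/2 = 50%. A respondent who always identifies tDCS and guesses the cognitive component also gets 50%. Split by component, the first is 100% right on cognitive intervention and 50% on tDCS, and the second is the reverse. The pooled count cannot tell them apart, but the collected data can.

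The reference proportion also matters. 50/100 against 25% gives (50 − 25)²/25 + (50 − 75)²/75 = 33.3, p about 8 × 10⁻⁹. The same count is exactly what a 50% reference would expect. The article names no reference proportion.

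**The case against.** **The text may condense a per-component question.** The article does not print the questionnaire, and Proposed Analysis describes the treatment condition factor by factor, as active or placebo for each. The full protocol's form may do the same. This limits the point to the wording as printed; if the form already asks about each component, only the text needs correcting. It does not remove the point, because the printed question and the printed error-or-correct scoring do not fit the four groups.

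**Only part of the check is affected.** This stands. Groups 1 and 4 can be scored without ambiguity, and relatives and patients are asked for the group. A reader might infer that the whole blinding assessment fails, or that it cannot inform the NPI-Q, DAD and Zarit. The article does not support that: those instruments rest on caregivers or informants, and relatives' group guesses can be split by component.

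**The test's null is not stated.** This also stands. One could argue that complete unblinding would pass unnoticed if the proportion correct were compared between arms, or that a blind rater who always answers active would look unblinded (75 v 25 against 50:50 on an any-active key: chi-square 25.0, p = 5.7 × 10⁻⁷). Both need a comparison or a reference value that the article does not specify, so neither describes what the plan will do.

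**Little depends on the result.** No threshold, decision or change of analysis is tied to the blinding check. That limits the weight of the point, but the change is nearly free.

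**Conclusion.** The point holds for the raters. As printed, their guess has no defined correct answer in groups 2 and 3, half the sample, and the chi-square depends on the key chosen. Raters who know only the tDCS allocation score anywhere from 50% to 100%; under the assumed partial-knowledge guesses, p runs from 1.0 to 2 × 10⁻⁹. The guess patterns are illustrative, but the dependence on the key follows from the design.

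The conclusion assumes that the printed wording reflects one two-way answer per patient, and that the raters questioned are those who carry out the outcome assessments. On that basis it bears on the ADAS-Cog and CSDD. For relatives and patients the question is usable; the weakness there is only that pooling into correct and incorrect, with chance at 25% and not 50%, discards component-level information.

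This is a supporting check. A reader should not infer that the primary ADAS-Cog analysis is invalid or needs changing.

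**What to change.** 1. **Raters.** Ask two questions: tDCS active or sham, and cognitive intervention active or placebo. Alternatively, ask for one of the four groups, as relatives and patients are asked.
2. **Analysis, all respondent types.** For each component, tabulate the guess against the true allocation (50 v 50) and test that association, or report a blinding index by arm. Use this in place of the pooled errors against correct responses, and carry it into the planned comparison by clinical response.
3. **If the form already asks by component,** correct the description under Randomization and Blinding to say so.

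The cost is one extra question at an interview already planned and two sentences of analysis text. The question has to change before the post-treatment interviews, because the component that a rater meant cannot be recovered afterwards.

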### Attrition and Adherence

Attrition will be considered under the following conditions: (a) two consecutive or three alternating absences from treatment sessions in a one-month period; (b) the inability to complete the post-test and follow-up; and (c) the development of any disabling condition preventing the participant’s participation in the study. Regarding adherence strategies, sessions missed until the established limit will be reset the following week. Flexible therapy hours will also be offered, and the relatives of the patients will be directly contacted by telephone to confirm the dates of evaluation, thereby reinforcing treatment adherence (Brunoni et al., 2011). Additional measures to avoid dropouts will also be applied, including periodic assessments of treatment satisfaction, discussion of difficulties in continuing treatment (for example, logistics of the trips to the laboratory) and attempts to resolve and avoid possible problems that may affect adherence to and continued participation in the study.

